## Methods

### Study Design

CLARITY is a 3-year prospective, multisite, observational study of 2000 participants with a matched control, measuring the impact of real-time patients’ MRSB and the OmniGraf biomarker panel on change in renal function over time. Approximately 50 sites will be targeted to enroll participants. The targeted sites will include transplant centers and large community nephrology practices with large populations of kidney transplant recipients who fall within the time line of 3 months to 2 years post transplantation. Sites will be limited to 200 participants to limit center effects in our outcomes.

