### Statistical Analysis

#### Sample Size Requirements

Sample size was determined using an SAS macro program, %GFR_Slope_Power, developed by Vonesh et al [14] specifically for the purpose of determining sample size or power estimates for comparing slopes between 2 treatment groups based on the linear spline mixed-effects model. An Assumption of eGFR slope change over 3 years in standard care was adopted in accordance with Vincenti et al [15]. Collectively, it is estimated that a sample of 450 patients per protocol would be required to detect a minimum total slope difference at 1.08 mL/minute/1.73 m^2^/year with 84% power, assuring that the study will be powered for a clinically meaningful difference of 5 mL/minute/1.73 m^2^/year. Conservatively assuming a 50% dropout rate and 50% loss to follow-up or missing data for end of follow-up, for this analysis, a sample size of 2000 participants should be sufficient to demonstrate a clinically significant difference in the primary outcome. Annual and as-needed review by an advisory board will halt enrollment when it is predicted that the sample size will be met.

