#### Primary Analysis

The primary outcome variable defined is a change in the slope of eGFR in participants enrolled in the study compared to that of a matched cohort. Matching variables will include sex, race, time from transplant, living or deceased donor, and baseline eGFR.

eGFR will be summarized using descriptive statistics by study visit. Plots will be used as a general guideline to assess the functional relationship of eGFR over time for modeling purposes. Change in eGFR across time will be modeled using a linear mixed-effects (random intercept random slope) model.

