Physicians can use the MRSB and OmniGraf results as they see fit, along with other clinical laboratory tests and information; however, they will be provided with a potential framework for integrating the information into their practice (Figure 1). In short, clinicians will see participants and review the MRSB portal and clinical laboratory tests, including OmniGraf. If the clinician notes that the participant has less than ideal renal function or has an MRSB that is troubling him/her, a discussion can be had between the clinician and participant. A clinical workup for the renal function or ADE can be performed to identify other treatable causes. If it is determined that the ADE (including renal function) is caused by or exacerbated by medications that the participant is taking, the laboratory findings and OmniGraf biomarker results can be used within the clinician-participant discussion to help determine the risks and benefits of adjusting medications to mitigate the ADE. OmniGraf results can also provide additional information to clinicians regarding participants who do not have a low eGFR or ADE, assisting in their clinical decision-making or identifying participants who may be at risk of subclinical inflammation.

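### The 200-per-site cap limits dominance by one site but does not account for within-site correlation of eGFR slopes, and the stated primary model names no site level

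*Protocol article*

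**What the plan says.** Under Study Design, the protocol article sets the number of sites and the cap: "Approximately 50 sites will be targeted to enroll participants", and "Sites will be limited to 200 participants to limit center effects in our outcomes". No other measure against center effects appears. The sites are to be a mix of transplant centers and large community nephrology practices.

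Under Primary Analysis: "Change in eGFR across time will be modeled using a linear mixed-effects (random intercept random slope) model". The sentence does not give the level of the random effects and does not mention site. The matching variables are sex, race, time from transplant, donor type and baseline eGFR; center is not among them. Under Study Endpoint Definitions and Assessment Plan, the controls are a propensity-matched cohort from the US Medicare database.

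Under Sample Size Requirements, "a sample of 450 patients per protocol would be required to detect a minimum total slope difference at 1.08" mL/min/1.73 m² per year "with 84% power, assuring that the study will be powered for a clinically meaningful difference of 5". After attrition, "a sample size of 2000 participants should be sufficient to demonstrate a clinically significant difference in the primary outcome". No site correlation or design effect is mentioned.

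Under Resources and Biomarker Testing: "Physicians can use the MRSB and OmniGraf results as they see fit". The framework offered to them is optional, and biomarker testing follows each participant's standard-of-care laboratory frequency.

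**The concern.** The article raises center effects itself and answers them only with a recruitment rule. A ceiling on site size controls how much weight one site can carry. It does nothing about participants at the same site having similar slopes, which is a matter for the model and for the power calculation.

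Slopes could plausibly cluster by site here. Use of the biomarker and symptom reports is left to the clinician, testing frequency follows local practice, and two types of practice are mixed.

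The external control group makes this matter more. In a trial randomized within sites, a site's influence on slope is shared by both arms and largely cancels. Here the study sites exist only on the participant side, so between-site variation passes directly into the error of the slope difference. If slopes vary by site and the analysis ignores it, the primary confidence interval is too narrow. The 84% power also carries no stated allowance for this variation.

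**Working it through.** **Inputs from the article.** 2000 participants; about 50 sites; cap of 200; 450 patients per protocol; detectable slope difference 1.08 mL/min/1.73 m² per year; power 84%; 50% dropout and a further 50% loss or missing data.

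**Assumptions, because the article does not give them.** 450 is per group; the test is two-sided at 0.05; controls are unclustered; attrition is equal across sites; the intraclass correlation (ICC) of participant slopes is 0 to 0.05.

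**Step 1: the plan's own figures.** Applying both losses, 450 / (0.5 × 0.5) = 1800, and 2000 × 0.25 = 500 evaluable. So 2000 covers 450 with a margin but is not an exact reproduction. The 84% cannot be recomputed because no slope SD is given; it can only be inverted:
- SE of the difference = 1.08 / (1.960 + 0.994) = 0.366
- slope SD = 0.366 / √(2/450) = 5.48 mL/min/1.73 m² per year (3.88 if 450 is the total of both groups)

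**Step 2: how tight the cap is.** The mean site size is 2000 / 50 = 40. The cap is 200 / 40 = 5 times that, and 200 / 2000 = 10% of the sample. At the cap, 2000 / 200 = 10 sites could fill the study. The size-weighted mean cluster size, Σm² / Σm, is 40 with 50 even sites and 200 with ten full sites. It would be about 510 if one uncapped site enrolled 1000 and 49 sites shared the rest. So the cap does bound clustering, at up to five times that of an even spread.

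**Step 3: effect on the slope comparison.** With m evaluable participants per site:
- design effect in the participant arm: DE = 1 + (m − 1) × ICC
- SE multiplier for the difference (equal groups, one arm clustered): r = √((DE + 1) / 2)
- type I error if site is ignored: 2 × (1 − Φ(1.96 / r))
- power if site is allowed for: Φ(1.08 / (0.366 × r) − 1.96)

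Fifty even sites give m = 450 / 50 = 9 or 500 / 50 = 10. Ten full sites give m = 45 or 50. Power uses the 450-per-group SE throughout.

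| Sites | m | ICC | DE | r | Type I error, site ignored | Power, site allowed for |
|---|---|---|---|---|---|---|
| any | any | 0 | 1.00 | 1.00 | 5.0% | 84% |
| 50 even | 9 | 0.01 | 1.08 | 1.02 | 5.5% | 82.6% |
| 50 even | 9 | 0.05 | 1.40 | 1.10 | 7.4% | 76.9% |
| 50 even | 10 | 0.01 | 1.09 | 1.02 | 5.5% | 82.4% |
| 50 even | 10 | 0.05 | 1.45 | 1.11 | 7.7% | 76.1% |
| 10 full | 45 | 0.05 | 3.20 | 1.45 | 17.6% | 53.1% |
| 10 full | 50 | 0.01 | 1.49 | 1.12 | 7.9% | 75.4% |
| 10 full | 50 | 0.05 | 3.45 | 1.49 | 18.9% | 50.8% |

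Worked case (m = 10, ICC 0.05): DE = 1 + 9 × 0.05 = 1.45; r = √(2.45 / 2) = 1.107; type I error = 2 × (1 − Φ(1.771)) = 7.7%; power = Φ(1.08 / 0.405 − 1.96) = Φ(0.71) = 76%.

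The last two columns describe different analyses. One ignores site and pays in type I error; the other allows for site and pays in power. They are not two losses suffered together.

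**Step 4: what the ICC range means.** With a slope SD of 5.48, an ICC of 0.01 is a between-site SD of √0.01 × 5.48 = 0.55 mL/min/1.73 m² per year, and 0.05 is √0.05 × 5.48 = 1.23. The upper end would therefore mean that sites differ by slightly more than the 1.08 the study is sized to detect.

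**The case against.** The strongest objection is that this is a condensed article without its statistical analysis plan. A reader might infer that site is excluded from the primary model. The article does not say so: it names a model type in one sentence and leaves the level of the random effects open. A site random effect or clustered variance is often specified later, and its absence alone would be no finding. That stands, so the point is not that site has been ruled out. What remains is that the article names center effects as a threat and gives a cap as its only answer, beside a model and a power statement that do not mention site.

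A reader might also infer that the cap does nothing, or that the standard error is certainly too small. Neither follows. The cap holds any site to 10% of the 2000. The standard error is too small only if slopes vary between sites and the analysis ignores it; at an ICC of 0 nothing changes. The article gives no ICC. Clinician discretion makes between-site variation plausible but does not demonstrate it.

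The ten-site figures should not be taken as the expected case, because the plan is for about 50 sites.

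Power is also not at risk at the difference the article calls clinically meaningful. At 5 mL/min/1.73 m² per year, even the largest SE in the table (0.366 × 1.49 = 0.545) leaves power above 99.9%. That stands too. The loss of power concerns the 1.08 difference to which the 84% is attached, while the interval width matters whatever the true difference is.

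**Conclusion.** The point holds in a limited form. The cap limits dominance by one site and is not an adjustment for correlated slopes within sites. The primary model as described names no site level, and the external control group means site variation does not cancel.

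On the planned spread of about 50 even sites, the effect is modest. Type I error is 5% to about 7.7% if site is ignored; power at 1.08 is 84% down to about 76% if it is allowed for. Ten sites at the cap sets the upper bound, with type I error up to about 19% or power down to about 51%. These ranges rest on an assumed ICC of 0 to 0.05, 450 per group, a two-sided 0.05 test, unclustered controls and even attrition. This should be settled before the analysis; it does not invalidate the design.

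**What to change.** 1. In the primary analysis, add a site-level random intercept and random slope for participants. This should be a partially nested model, with controls not assigned to any study site. A fixed site effect would not work, because site cannot be separated from group. The alternative is standard errors clustered by enrolling site, with each control as its own cluster. The unit should be the enrolling site rather than the transplant center, since some sites are community practices.
2. Under Study Design, say that the cap limits dominance by one site and is not the adjustment for center effects.
3. Under Sample Size Requirements, restate the 84% power over an assumed range of site correlation, and say whether 450 is per group.

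The cost is small: the enrolling site of each participant should already be known, so no new data are needed. The model does need a rule for handling controls, so it is slightly more than one extra term. The downside is a somewhat wider interval, about 2% to 11% on the planned spread at ICC 0.01 to 0.05 and up to about 49% at the ten-site bound, and a less favorable stated power.

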### Ethical Considerations

The study is under review by the Central Institutional Review Board (Pro00067364) as well as local institutional review boards (IRBs) at some sites (depending on local IRB requirements) and conforms to the ClinicalTrials.gov guidelines.

### Aims

The primary objective is to evaluate change in renal function over time in kidney transplant recipients who are undergoing OmniGraf monitoring in conjunction with MRSB monitoring. A secondary objective of this study is to identify the impact of OmniGraf use, in conjunction with patient-reported MRSB, as part of clinical care on patient quality of life and patient and graft survival.

### Recruitment, Screening, and Enrollment Procedures

Adult (≥18 years old) kidney transplant recipients between 3 months and 2 years post transplantation, who meet the study eligibility criteria will be identified in accordance with local site IRB-approved practices and approached by research personnel for consideration for participation. Potential participants will be required to go through an informed consent process and complete an informed consent document to ensure they understand the goals, risks, and potential benefits of the study before any research-related activities are carried out.

### Eligibility

#### Inclusion Criteria

Participants must be adult (≥18 years of age) recipients of a primary or subsequent kidney transplant, between 3 months and 2 years post transplantation, selected by their provider to undergo OmniGraf testing as part of posttransplantation care, and provide written informed consent and Health Insurance Portability and Accountability Act authorization.

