Clinicians also find themselves in a clinical quandary when faced with patients with poor graft function. According to the most recent Organ Procurement and Transplantation Network and Scientific Registry of Transplant Recipients Annual Data Review [5], 50% of kidney transplant recipients have stage 3 chronic kidney disease (CKD) or worse at 1 year post transplantation. A large international analysis by the Patient Outcomes in Renal Transplantation investigators demonstrated that patients with stage 3b CKD or lower at 1 year post transplantation were at a significantly higher risk of graft failure by 10 years post transplantation—a risk that increased with a decrease in the estimated glomerular filtration rate (eGFR) [10]. Clinicians are aware of this, but they must also consider the risk of acute rejection that increases whenever immunosuppression is altered.

The OmniGraf biomarker panel (Transplant Genomics, Inc) includes the TruGraf peripheral blood expression profile and the Viracor TRAC donor-derived cell-free DNA test, which have demonstrated a strong ability to identify immune quiescence in stable patients post kidney transplantation, with a negative predictive value of 94% when both tests are negative and a positive predictive value of 89% for subclinical rejection when both tests are positive [11,12].

Because of the strong “rule out” capabilities of OmniGraf, it would be an ideal complement to real-time ADE knowledge and eGFR awareness to help guide clinicians’ decisions to adjust (or not) the immunosuppressive regimen and help provide a dialogue between patients and clinicians on the risk-benefit of medication adjustments. With its ability to both “rule out” and “rule in” subclinical rejection, it would also be an ideal tool to help monitor patients during and after medication adjustments. Allowing patients to express their ADEs and the impact they have on their lives, along with frank discussions with clinicians and risk-benefit of medication adjustments, may help increase patient engagement and activation. This is a key goal to help minimize the burden of symptoms and increase life participation [13].

Therefore, the aim of this study is to evaluate change in renal function over time in kidney transplant recipients who are undergoing OmniGraf monitoring in conjunction with patients’ medication-related symptom burden (MRSB) monitoring.

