#### Exclusion Criteria

Patients who are recipients of a combined organ transplant with an extrarenal or islet cell transplant, previous recipients of a nonrenal solid organ or islet cell transplant, those known to be pregnant, those infected with HIV, those who have active BK nephropathy, those who have nephrotic range proteinuria, or those who are participating in other biomarker clinical trials at the time of assessment will be excluded from participation.

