### Resources and Biomarker Testing

Participants will be provided with access to a method of reporting real-time MRSB via smartphone app or the internet and instructed to answer the MRSB questionnaire whenever they are experiencing ADE or prior to clinic visits (Textbox 1). The MRSB questionnaire is based on side effects that have been considered in previously validated side effect measures and is based on a questionnaire used in a mobile health analysis that was found to reduce hospitalizations and grade 3 or higher ADEs [9].

Physicians will have access to a portal that will include an easy-to-read report of responses, simultaneously prioritizing frequent MRSB that the participant considers at least moderately troubling. Participants will also undergo OmniGraf biomarker testing based on the frequency of their standard of care laboratory testing (Table 1). Laboratory testing data are not mandated and will be collected and entered into the electronic case report forms if available in the patient record.

Medication-related symptom burden questionnaire.

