### Study Endpoint Definitions and Assessment Plan

The following will be used to define and assess events within this study.

The primary endpoint is a comparison of the slope change in eGFR from baseline to the end of follow-up between the study participants and a matched control group. eGFR will be calculated using the 4-variable Modification of Diet in Renal Disease equation [16], with a sensitivity analysis performed using the Chronic Kidney Disease Epidemiology Collaboration equation [17]. Routine serum creatinine concentrations, which are measured as a part of usual care, will be utilized to estimate the GFR at baseline and at months 12, 24, and 36 post enrollment for assessments. The slope in eGFR change will be calculated for the entire follow-up for the primary outcome, with subanalyses performed between the other described time points. The matched control group will be a propensity-matched cohort from the US Medicare database.

Furthermore, we will compare the PROMIS Self-Efficacy for Managing Chronic Conditions–Managing Medications and Treatment–Short Form 4a scores at the end of follow-up relative to baseline [18]. This will measure changes in self-efficacy within the participant population—the belief that one can carry out a behavior necessary to reach a desired goal, even when a situation contained unpredictable and stressful elements. The study coordinator will provide access to the survey at baseline and at months 12, 24, and 36 post enrollment. Subanalyses will be performed among all time points.

We will then compare the PROMIS-29 Profile (version 2.1) scores at the end of follow-up relative to baseline [19]. This will measure changes in overall quality of life and satisfaction. The study coordinator will provide access to the survey at baseline and at months 12, 24, and 36 post enrollment. Subanalyses will be performed among all time points.

This will be followed by a comparison of the PROMIS Depression Scale scores at the end of follow-up relative to baseline [20]. This will measure changes in symptoms of depression. The study coordinator will provide access to the survey at baseline and at months 12, 24, and 36 post enrollment. Subanalyses will be performed among all time points.

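### Provider-selected entry with no stability requirement permits indication-driven selection, which the five named matching variables cannot remove from the primary eGFR slope comparison

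*Protocol article*

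**What the plan says.** **Entry.** Under Inclusion Criteria, an adult recipient between 3 months and 2 years after transplant qualifies when "selected by their provider to undergo OmniGraf testing as part of posttransplantation care". Among signs of graft trouble, the Exclusion Criteria name only "those who have active BK nephropathy, those who have nephrotic range proteinuria". A recent rejection or a rising creatinine does not exclude.

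**Test rationale.** The Introduction cites the panel's two components as tests "which have demonstrated a strong ability to identify immune quiescence in stable patients post kidney transplantation".

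**Testing in the study.** Under Resources and Biomarker Testing: "Participants will also undergo OmniGraf biomarker testing based on the frequency of their standard of care laboratory testing".

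**Controls.** Under Study Endpoint Definitions and Assessment Plan: "The matched control group will be a propensity-matched cohort from the US Medicare database". Under Primary Analysis: "Matching variables will include sex, race, time from transplant, living or deceased donor, and baseline eGFR".

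**Endpoint.** "The primary endpoint is a comparison of the slope change in eGFR from baseline to the end of follow-up", between participants and matched controls. Creatinine from usual care is used "to estimate the GFR at baseline and at months 12, 24, and 36 post enrollment for assessments". The model is linear with random intercept and slope.

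**Baseline.** Table 1 gives the baseline visit a window of days -90 to 0 and collects clinical events, including rejections, at that visit.

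**The concern.** Participants are in the study because a clinician decided to order a test. The article describes no such decision for the controls. If the decision is sometimes prompted by a change in the graft, participants and controls with the same baseline eGFR are not alike: one may be temporarily low, the other low for a long time. The primary slope starts at the same baseline used for matching, so rebound from a temporary dip would be credited to OmniGraf plus MRSB monitoring. If the prompt was instead the start of a lasting decline, the comparison would be biased against the study group.

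Baseline eGFR is the only renal-function variable in the named matching set. It cannot tell these two situations apart, or either of them from routine surveillance.

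**Working it through.** **1. The plan's own figures.** Sample Size Requirements gives 450 patients, a slope difference of 1.08 mL/min/1.73 m²/year and 84% power. It gives no significance level or slope SD, and does not say whether 450 is per group or in total, so the 450 cannot be reproduced independently. Assuming a two-sided 5% test, the implied standard error of the slope difference is 1.08 / (1.960 + 0.994) = 0.366. This is used below only as a scale. The two stated 50% losses leave 2000 × 0.5 × 0.5 = 500 evaluable.

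**2. Weight of baseline in the slope.** Visits are at t = 0, 1, 2, 3 years, with mean 1.5 and Σ(t - 1.5)² = 2.25 + 0.25 + 0.25 + 2.25 = 5. The least-squares weights are (t - 1.5)/5 = -0.3, -0.1, +0.1, +0.3.

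**3. Effect of a temporary dip.** If a share f of participants has baseline eGFR lowered by d, with recovery by month 12, the group slope rises by about 0.3 × f × d. With d = 10 (assumed):

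| f (assumed) | Added slope per year | Share of 1.08 |
|---|---|---|
| 0% | 0 | 0% |
| 10% | 0.3 | 28% |
| 20% | 0.6 | 56% |
| 30% | 0.9 | 83% |

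The added slope equals 1.08 when f × d = 1.08/0.3 = 3.6, for example 36% of participants with a 10-unit dip.

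**4. Does matching remove it?** A simulation with no treatment effect matched each participant to the nearest control on observed baseline eGFR. Assumed values were mean eGFR 55, between-patient SD 15, within-patient SD 4 or 7, mean slope -1.5 and slope SD 1.5. Rejection rates use a nominal 5% test and the standard error from step 1.

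| f, d (assumed) | False slope difference per year | Rejection rate |
|---|---|---|
| 0%, any | 0 (within 0.03) | about 5% |
| 10%, 5 | 0.09 to 0.16 | about 6 to 7% |
| 10%, 10 | 0.24 to 0.29 | about 10 to 13% |
| 25%, 10 | 0.61 to 0.68 | about 39 to 46% |
| 25%, 15 | 0.93 to 1.04 | about 72 to 81% |

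Matching removes only a little. Controls picked at a low observed value also recover somewhat, by the fraction of baseline variance that is noise. For 25% and 10 units, 0.75 × 225/(225 + 16) = 0.70 and 0.75 × 225/(225 + 49) = 0.62, in line with the simulation.

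**5. Mixed model.** One simulated data set of 2000 matched pairs (25%, 10 units, within-patient SD 5) gave a slope difference of 0.77 with a random-intercept, random-slope model, the same as the mean of the least-squares slopes. That fit raised a convergence warning, so it only supports step 3.

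**6. The opposite sign.** If a share f instead has an extra persistent decline of g per year, the group slope changes by about -f × g. Simulated values for g = 1 to 3 were -0.25 to -0.76 at f = 25% and -0.50 to -1.50 at f = 50%.

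**The case against.** **For-cause entry is not stated.** A reader might infer that patients tested for cause do enter at an atypical eGFR, so that a slope difference is built into the endpoint. The article does not say so. It speaks of testing as part of care, ties study testing to the standard-of-care laboratory schedule, and uses the term for-cause only for biopsies. This stands in full: the text permits such entry but does not describe it. The laboratory schedule governs how often enrolled patients are tested, however, not why the provider chose them. The Introduction also presents the panel as an aid for clinicians faced with poor graft function.

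**A single day-0 value is a reading.** The article says only baseline eGFR, within a 90-day window. Averaging several values in that window could shrink d. This stands, and d should be read as the deviation in whatever baseline value is used.

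**Matching detail belongs in the full protocol or analysis plan.** The article's verb is that matching variables will include five items, which may not be exhaustive. This holds for calipers, index-date rules and similar detail. But the article does name a set, and following that set as written leaves the reason for selection uncontrolled.

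**Test performance in stable patients.** A reader might infer that a broader population undermines the study. It does not: diagnostic accuracy is not an endpoint, and this is an observational study of use in care. The mismatch is a caution about the rationale, not a fault in the slope comparison.

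**Restricting the primary analysis to stable entrants.** This would cost power. From 500 evaluable, removing 10% leaves 450 and removing 20% leaves 400, below the stated requirement. At 400, power is about 80% under the assumptions of step 1. The stability definition would also have to come from cited sources that the article does not reproduce. The objection stands, so the fix does not restrict the primary population.

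**Conclusion.** The concern holds in conditional form. The entry rule permits indication-driven selection, and the five named matching variables cannot remove the resulting regression to the mean or difference in trajectory. Its possible size matters: about 0.3 × f × d per year, or 0.3 to 0.9 for an assumed 10-unit dip in 10% to 30% of participants, against 1.08. It is negligible if few enter this way and negative if selected patients keep declining.

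The article gives neither the share, the size nor the direction, so it does not support a claim that the result will be biased in favour of OmniGraf. The conclusion is that, as planned, a positive result could not be told apart from recovery after a dip, nor a null result from adverse selection. The figures assume eGFR at the four stated time points, complete data, and dips that resolve by month 12. The rejection rates also assume a two-sided 5% test. A correction is worth making because it is cheap and the reason for testing is best captured at enrollment.

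**What to change.** 1. Keep the full cohort as the primary population.
2. Add one eCRF field at enrollment for the reason OmniGraf was selected: routine surveillance or clinical trigger.
3. Under Primary Analysis, add treated rejection before the index date to the matching variables, and the pre-index eGFR trend where the control source holds it. Rejections are already collected for participants at baseline in Table 1. The article does not show whether serial creatinine is available for controls, so the trend is conditional on that.
4. Prespecify two sensitivity analyses of the primary slope comparison: (a) surveillance-only entrants with their matched controls; (b) the slope starting at month 12 instead of at the matched baseline.

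**Cost.** One data field, slightly harder matching, and lower precision in the sensitivity analyses. For (b), visits at years 1, 2 and 3 give Σ(t - 2)² = 2 instead of 5, so the part of the slope variance due to measurement noise is 5/2 = 2.5 times as large, and any effect in the first year is lost. Analysis (b) addresses temporary dips only; for persistent decline, the protection comes from the added matching variables and analysis (a).
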